## Abstract

**Background:**

Acupuncture is widely used in China to treat functional dyspepsia (FD). However, its effectiveness in the treatment of FD, and whether FD-specific acupoints exist, are controversial. So this study aims to determine if acupuncture is an effective treatment for FD and if acupoint specificity exists according to traditional acupuncture meridians and acupoint theories.

**Design:**

This multicenter randomized controlled trial will include four acupoint treatment groups, one non-acupoint control group and one drug (positive control) group. The four acupoint treatment groups will focus on: (1) specific acupoints of the stomach meridian; (2) non-specific acupoints of the stomach meridian; (3) specific acupoints of alarm and transport points; and (4) acupoints of the gallbladder meridian. These four groups of acupoints are thought to differ in terms of clinical efficacy, according to traditional acupuncture meridians and acupoint theories. A total of 120 FD patients will be included in each group. Each patient will receive 20 sessions of acupuncture treatment over 4 weeks. The trial will be conducted in eight hospitals located in three centers of China. The primary outcomes in this trial will include differences in Nepean Dyspepsia Index scores and differences in the Symptom Index of Dyspepsia before randomization, 2 weeks and 4 weeks after randomization, and 1 month and 3 months after completing treatment.

**Discussion:**

The important features of this trial include the randomization procedures (controlled by a central randomization system), a standardized protocol of acupuncture manipulation, and the fact that this is the first multicenter randomized trial of FD and acupuncture to be performed in China. The results of this trial will determine whether acupuncture is an effective treatment for FD and whether using different acupoints or different meridians leads to differences in clinical efficacy.

**Trial registration number:**

Clinical Trials.gov Identifier: NCT00599677.

## Background

Functional dyspepsia (FD) is defined as chronic upper abdominal discomfort or pain, heartburn, early satiety, nausea, vomiting, abdominal distension and bloating, without any apparent organic, systemic, or metabolic pathology to explain these symptoms [1-3]. An epidemiological survey of Western countries showed that the prevalence of FD ranges from 11.5% to 14.7% [4]. An additional study conducted in Tianjin, China, revealed that 23.29% of the population suffers from FD [5]. A common and well-recognized public health problem, FD reduces patient quality of life and increases the economic burden of medical care [6-11].

Although several classes of drugs (such as proton pump inhibitors, H2-blockers, and prokinetic drugs) have been used in clinical practice and some (such as antisecretory agents or prokinetics) have been effective in placebo-controlled trials, only a small proportion of patients report sufficient relief from these treatments [12].

The exact etiology of FD remains unclear; thus, it is not surprising that current treatments for FD are of limited efficacy and that alternative therapies, including acupuncture, are attractive to both patients and practitioners [13]. Acupuncture has been used in China for many years to treat gastrointestinal symptoms, including acute and chronic gastroenteritis, diarrhea, constipation and gastroduodenal ulcers [14]. Several randomized controlled trials (RCTs) have suggested that acupuncture is an effective treatment for FD, particularly with regards to dyspeptic symptoms, belching and anorexia [15-17]. However, it has been difficult to draw firm conclusions from the results of these RCTS due to the poor quality of the studies and the small sample sizes. Therefore, the mechanisms by which acupuncture treat FD, or whether this therapy works at all, remain the subject of debate. Therefore, we have designed a multicenter randomized controlled trial to address these problems and provide more conclusive data on the use of acupuncture to treat FD.

The first aim of this trial will focus on the efficacy of acupuncture as a treatment for FD. Second, we will attempt to determine if the efficacy of acupuncture differs with the type of acupoint, or with the use of acupoints for different meridians. In a separate paper, we have described the methods of a clinical trial to examine the role of acupuncture in managing migraines [18], and we are currently conducting a similar study to assess the efficacy of acupuncture as a treatment for migraines.

## Methods

### Study design

This study will consist of a multicenter randomized controlled trial to compare four acupoint treatment groups with one non-acupoint control group and one drug (positive control) group (Figure 1, Table 1). This trial will be completed in eight hospitals, including the First Affiliated Hospital of Chengdu University of Traditional Chinese Medicine (TCM), People's Hospital of Sichuan Province, No. 4 People's Hospital of Sichuan Province, Affiliated Hospital of Ningxia Medicine University, First Affiliated Hospital of Hunan University of TCM, No. 1 People's Hospital of Wuhan City, TCM Hospital of Hubei Province, and the TCM Hospital of Wuhan City.

**Table 1 T1:** Time to visit and data collection

	-1 week	0 week	2 week	4 week	1 month after Treatment Phase	3 months after Treatment Phase
			
	Baseline	Treatment phase			Follow-up Phase	
**Patients**						
Informed consent	X					
Medical history	X					
Physical examination	X					
Randomization		X				
						
**Interventions**						
Specific acupoints of Stomach meridians(n = 120)						
Non-specific acupoints of Stomach meridians(n = 120)		20 sessions of acupuncture at acupoints				
Acupoints of Shu and Mu acupoints(n = 120)						
Acupoints of Gallbladder meridians(n = 120)						
						
**Comparisons**						
Non-acupoints control group(n = 120)		20 sessions of acupuncture at non-acupoints				
Itopride control group(n = 120)		50 mg three times daily, 20 days treatment				
						
**Outcomes**^a^						
NDI		X	X	X	X	X
SID		X	X	X	X	X
SF-36		X		X	X	X
						
**Participants safety**						
Laboratory test		X		X		
Adverse events		X	X	X	X	X

a. NDI = Nepean Dyspepsia Index; SID = Symptom Index of Dyspepsia; SF-36 = Mos 36-item Short Form Health Survey

**Figure 1 F1:**
[figure not shown]
**Trial flow chart**.

This trial will include a 4-week treatment period and a 3-month follow-up period. After randomization, patients will receive 20 treatments over a period of 4 weeks. Outcome measurements will be assessed at baseline (i.e., 1 week after subjects are diagnosed with FD), as well as 2 weeks and 4 weeks after randomization, and 1 month and 3 months after conclusion of the treatment phase. Patients will be informed that they may be assigned to an acupuncture group, a non-acupoint control group, or the itopride control group.

This trial will be performed according to the principles of the Declaration of Helsinki (Version Edinburgh 2000). The study protocol has been approved by regional ethics review boards, including the national review board for clinical drug research, located in the Chengdu University Hospital of Traditional Chinese Medicine. This study protocol has permission number 2007 KL-002. All patients will be asked to provide written consent before enrollment, and will be given ample time to decide if they wish to participate and sign the consent form. For subjects who do not want to participate in acupuncture, other treatment options will be available.

### Randomization

A central-randomization scheme will be performed at the Chengdu Good Clinical Practice (GCP) Center, which is affiliated with the National Clinical Trial Center of Chinese Medicine. This scheme will be used to assign patients to one of six groups in a 1:1:1:1:1:1 ratio. A permuted-block randomization procedure, which is automatically under the control of a central computer system, will be used to generate an allocation sequence and blind researchers to the group assignments. Patients who meet the inclusion criteria will be referred to acupuncturists at one of the eight study hospitals. The cell phones of all acupuncturists will be approved and assigned specific ID numbers after the acupuncturist completes a special training course designed for this trial. The acupuncturists will then use the registered cell phones to send randomization information to the GCP Center. This randomization information will include the subject's name in a pinyin format, the subject's numerical birthday and the subject's gender. Once the GCP Center computer system receives the randomization information, it will randomly assign patients to an acupoint treatment group or to the control group. Random numbers and group assignments will be sent from the GCP Center to the acupuncturists via e-mail or short message service (SMS). This procedure will ensure adequate randomization concealment. Patients will be blinded to the type of acupuncture treatment they receive.

### Blinding

As the acupuncturists are responsible for sending randomization information and receiving notices of group assignments, it would not be practical to blind the acupuncturists to treatment allocations and patients' symptoms. Additionally, it is not possible to prevent patients from knowing if they have received acupuncture or itopride treatment. However, it is feasible and ethical to blind patients to the type of acupuncture they receive. In addition, we intend to conceal the group assignments from outcome assessors and our statistician. To assist with the blinding procedure, we named the groups A, B, C, D, E, and F in the medical records and case report forms (CRFs). The specific acupoints (or non-acupoints) will not be mentioned in these forms.

### Eligibility

#### Inclusion criteria

According to the Rome III Diagnostic Criteria for Functional Gastrointestinal Disorders [19], FD can be diagnosed by: (1) meal-induced dyspeptic symptoms (PDS); and (2) epigastric pain (EPS). Patients diagnosed with PDS or EPS will be considered for inclusion in this trial. Patients with one or more of these symptoms (such as postprandial fullness, early satiation, or epigastric pain or burning) will be considered patients with dyspepsia. Accordingly, the inclusion criteria for this study are consistent with the diagnostic criteria for functional dyspepsia: aged between 18 and 65 years; not received gastroenteric dynamic drugs in the 15 days before enrollment; not be taking part in any other clinical trials; and provide written informed consent.

#### Exclusion criteria

Patients with any of the following conditions will be excluded: contraindications to itopride, unconsciousness, history of mental disorders, aggravating malignant tumors or other serious consumptive disease, susceptibility to infection and bleeding, serious diseases of the cardiovascular, hepatic, renal, gastrointestinal, hematological systems, pregnancy or lactation.

### Recruitment strategies

#### Hospital-based recruiting

A large number of patients with FD are currently receiving healthcare or seeking health advice at hospitals in China. The host institution developed collaborations with eight additional hospitals. Primary care physicians at these hospitals are familiar with the study inclusion and exclusion criteria. Interested patients will be referred to specific researchers at a study hospital, who will obtain informed consent and conduct the screening evaluations. Patients who are willing to participate and who satisfy the inclusion criteria will be introduced to acupuncturists at the eight hospitals.

#### Television and newspaper advertisements

Television advertisements will be broadcast on local channels to promote study participation. Advertisements will also be published in local newspapers. Printed recruitment posters will be posted in the eight participating hospitals.

### Interventions

Interventions were designed according to records in ancient books and according to recent studies of acupuncture as a treatment for FD. Itopride is a non-acupuncture treatment option in this trial. The acupuncture protocol was developed in consensus with Chinese acupuncturists and acupuncture experts, and is consistent with the STRICTA (standards for reporting interventions in controlled trials of acupuncture) guidelines for the performance of acupuncture studies [20].

### Rationale for selecting acupoints

The acupuncture treatment protocol is consistent with the principles of traditional acupuncture theories. These principles state that FD is in close proximity to the stomach meridian; hence, it is reasonable that the acupoint corresponding to the stomach meridian would be most effective at treating this condition. We also chose to study the gallbladder meridian because it is anatomically close to the stomach meridian and therefore may achieve similar effects. Furthermore, traditional acupuncture theories maintain that specific points convey specific therapeutic effects. Thus, the specific acupoint corresponding to the stomach meridian would be expected to be more effective than a non-specific acupoint of the same meridian. Therefore, we selected the most frequently used specific and non-specific acupoints of the stomach meridian, according to the results of a previous review of ancient and modern literature. According to traditional acupuncture theories, the alarm and transport points are considered specific points. Alarm points (Front-Mu points) are specific points on the chest or abdomen where the qi of the respective viscera are concentrated, whereas transport points (Back-Shu points) are specific points on the back where the qi of the visceral organs are infused. Both alarm points and transport points can be used to treat diseases of specific Zang-Fu organs; for example, Zhongwan (CV12) and Weishu (BL21) are the alarm and transport points of the stomach and can be used to treat diseases related to this organ. Thus, Zhongwan (CV12) and Weishu (BL21) were selected for use in one of the acupuncture treatment groups.

### Control groups

Because itopride (Shenzhen Tsinghua Yuanxing Pharmaceutical Co., Ltd.) is an effective treatment for FD [21], we chose to use this drug as a positive control. Patients in the positive control group will receive similar treatment sessions as acupuncture groups, with administration of 50 mg itopride, three times daily, taken half an hour before meals [21].

The locations of non-acupoints have been defined in the literature [22-24]. The locations and manipulations of acupoints and non-acupoints are shown in Table 2, Figure 2 and Figure 3.

**Figure 2 F2:**
[figure not shown]
**Locations of acupoints (acupuncture treatment groups)**. Acupoints of treatment group 1 are specific acupoints of Stomach meridian. Acupoints of treatment group 2 are non-specific acupoints of Stomach meridian. Acupoints of treatment group 3 are Alarm and transport points. Acupoints of treatment group 4 are acupoints of Gallbladder meridian.

**Figure 3 F3:**
[figure not shown]
**Locations of non-acupoints (acupuncture control group)**. Descriptions of locations non-acupoints are available at table 2.

**Table 2 T2:** Details of each group.

Group	Acupoints	Manipulation
**Treatment group 1** (specific acupoints of stomach meridian)	(1) Chongyang(ST42)	(1) is punctured perpendicularly 0.3–0.5 cun avoiding the artery
	(2) Fenglong(ST40)	(2) is punctured perpendicularly 1–1.5 cun
	(3) Zusanli(ST36)	(3) is punctured perpendicularly 1–2 cun
	(4) Liangqiu(ST34)	(4) is punctured perpendicularly 1–1.2 cun
**Treatment group 2** (non-specific acupoints of Stomach meridian)	(1) Tiaokou(ST38)	(1) is punctured perpendicularly 1–1.5 cun
	(2) Dubi(ST35)	(2) is punctured perpendicularly 0.5–1 cun
	(3) Yinshi(ST33)	(3) is punctured perpendicularly 1–1.5 cun
	(4) Futu(ST32)	(4) is punctured perpendicularly 1–2 cun
		
**Treatment group 3** (Alarm and transport point)	(1) Weishu(BL21)	(1) is punctured obliquely along the spine fo r 0.5–0.8 cun
	(2) Zhongwan(CV12)	(2) is punctured perpendicularly 1–1.5 cun
**Treatment group 4** (acupoints of Gallbladder meridian)	(1) Qiuxu(GB40)	is punctured perpendicularly 0.5–0.8 cun
	(2) Guangming(GB37)	(2) is punctured perpendicularly 0.5–0.8 cun
	(3) Yanglingquan(GB34)	(3) is punctured perpendicularly 1–1.5 cun
	(4) Waiqiu(GB36)	(4) is punctured perpendicularly 0.5–0.8 cun
		
**Non-acupoint group**	(1) At the medial arm on the anterior border of the insertion of the deltoid muscle at the junction of deltoid and biceps muscles	(1) is punctured perpendicularly 0.5–1 cun
	(2) Half between the tip of the elbow and the axillae	is punctured perpendicularly 0.5–1 cun
	(3) Ulnar side, half between epicodylus medialis of the humerus and ulnar side of the wrist	(3) is punctured perpendicularly 0.5–1 cun
	(4) The edge of tibia 1 to 2 cm lateral to the Zusanli(ST36) horizontally	(4) is punctured perpendicularly 0.5–1 cun

### Standardized protocol for acupuncture manipulation

Sterile disposable stainless steel needles (length: 25–40 mm, diameter: 0.25 mm; Hwatuo, Suzhou, China) will be used on patients in the acupuncture group. Except for the CV12 acupoint, all acupoints and non-acupoints will be punctured unilaterally, alternating between the left and the right to relieve the pain caused from the insertion of two needles into one acupoint. All acupoint and non-acupoint control groups will receive electro-stimulation of acupuncture points. The technique used in the non-acupoint control group will be the same as treatment groups, except that no attempt will be made to achieve the *Deqi *sensation. After the stimulation of each acupoint or non-acupoint, auxiliary needles (13 mm in length and 0.18 mm in diameter) will be inserted laterally (proximal limbs or trunk) into acupoints or non-acupoints to a depth of 2 mm without manual stimulation. Therefore, eight needles will be inserted into each patient. Transcutaneous electric acupoint stimulation (Han's acupoint nerve stimulator, HANS, Model LH 200A TENS, Nanjing, China) will be used for the electro-acupuncture stimulation of every acupoint or non-acupoint after needle insertion. Each acupuncture needle and its auxiliary needle will be connected to the HANS electrical leads for 30 minutes, with a stimulation frequency of 2/100 Hz. The stimulation intensity will vary from 0.1 mA to 1.0 mA for all patients. Electro-acupuncture will be used to ensure that patients in different acupuncture groups receive the same extent of stimulation, which will ensure consistency with regards to performance. Other interventions (such as moxibustion, cupping and herbs) will not be used.

Patients in the acupuncture treatment groups and the non-acupoint control group will receive a total of 20 treatments over a 4-week period. The treatments will be administered once per day, for 5 continuous days, with a 2 day rest interval. This treatment course was designed according to the acupuncture protocol used in Chinese clinical acupuncture practice. All acupuncture practitioners had undergone at least 8 years of acupuncture training and were qualified TCM doctors; indeed some were associate chief TCM doctors.

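### The stated eight needles per patient does not fit the two-point group 3, so that group's needle count and the equal-stimulation claim must be reconciled

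*Protocol article*

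**What the plan says.** The section on standardized acupuncture manipulation sets the needling rules for all acupuncture arms. Points other than CV12 are needled on one side, with sides alternating. Each acupuncture needle is paired with an auxiliary needle, and the pair is wired to the stimulator for 30 minutes. The section then concludes: "Therefore, eight needles will be inserted into each patient". It goes on: "Electro-acupuncture will be used to ensure that patients in different acupuncture groups receive the same extent of stimulation". The Discussion repeats the idea, saying that the device gives every patient an equal level of treatment.

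Table 2 lists four points each for groups 1, 2 and 4 and for the non-acupoint control. For group 3 (alarm and transport points) it lists two, BL21 and CV12. The section on the rationale for selecting acupoints confirms the pair: "Zhongwan (CV12) and Weishu (BL21) were selected for use in one of the acupuncture treatment groups".

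On the control arm, the needling section says: "The technique used in the non-acupoint control group will be the same as treatment groups, except that no attempt will be made" to obtain Deqi.

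The Statistical analysis section tests the acupoint groups against the non-acupoint control and against each other.

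**The concern.** The count of eight is presented as a consequence of the needling rules, and it applies to every patient. It follows for arms with four points but not for an arm with two. Two things are at stake.

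First, the article does not tell the eight hospitals unambiguously how many needles a group 3 patient receives, although standardized needling is put forward as a main feature of the trial.

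Second, equal stimulation across arms is the stated safeguard for comparing them. If group 3 has fewer stimulated sites, a poorer result there could come from less stimulation, and an equal result could hide an advantage of the points themselves. Either way, a group 3 contrast would no longer isolate point type. Whether acupoints have specific effects is one of the trial's declared aims, and the alarm and transport points are among those the Discussion names as most commonly used.

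**Working it through.** **Inputs**
- Points per arm (Table 2): group 1 has 4 (ST42, ST40, ST36, ST34); group 2 has 4 (ST38, ST35, ST33, ST32); group 4 has 4 (GB40, GB37, GB34, GB36); the non-acupoint control has 4; group 3 has 2 (BL21, CV12).
- Acupuncture needles per point (needling section): 1, with CV12 excepted from the one-sided rule.
- Auxiliary needles per acupuncture needle (needling section): 1.
- Sessions: 20.

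**Formulas**
- Needles per session = acupuncture needles x (1 + auxiliary needles per acupuncture needle).
- With one auxiliary each, stimulated pairs = acupuncture needles.

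**Reproducing the stated figure.** For groups 1, 2, 4 and the non-acupoint control: 4 x (1 + 1) = 8 needles and 4 pairs. The stated eight is reproduced exactly, which supports this reading of the rules.

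**Group 3 under each reading**

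| BL21 | CV12 | Auxiliaries per needle | Total | Fits the needling section? |
|---|---|---|---|---|
| 1 | 1 | 1 | 2 x 2 = 4 (2 pairs) | Yes |
| 1 | 2 | 1 | 3 x 2 = 6 (3 pairs) | Yes, if the CV12 exception means two needles |
| 2 | 1 | 1 | 3 x 2 = 6 (3 pairs) | No, BL21 is one-sided |
| 2 | 2 | 1 | 4 x 2 = 8 (4 pairs) | No, BL21 is one-sided |
| 1 | 1 | 3 | 2 x 4 = 8 | No, one auxiliary per needle |

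Eight can be reached, but only by breaking the one-sided rule for BL21 or the pairing of one auxiliary with each needle. The readings that keep both rules give 4 or 6.

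**Over a course of treatment.** 8 x 20 = 160 insertions in the four-point arms. Group 3 has 4 x 20 = 80, or 6 x 20 = 120 on the wider reading of the CV12 exception.

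**Which comparisons are touched.** Those are group 3 against groups 1, 2 and 4, and group 3 against the non-acupoint control. Groups 1, 2 and 4 have the same needle count as each other and as the control.

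**The case against.** The strongest reply is that eight may be what was intended, with Table 2 or the one-sided rule imprecise for group 3. If the investigators confirm eight needles and four pairs, the imbalance disappears. That stands, and it is why the consequences below are conditional. It does not remove the contradiction, because the text as published cannot yield eight for this arm. A broken table is not the explanation either, since the rationale section names the same two points. Figure 2, which shows the point locations, was not available for this review.

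A second reply is that the equal-stimulation statement is about replacing manual technique with a device, so that practitioners perform alike. That is a fair account of its purpose. But the sentence speaks of what patients in different groups receive, and it does not hold per patient if one arm has two or three stimulated pairs and the others four.

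Several stronger readings are tempting and are not supported:
- **Group 3 gets exactly half the exposure.** This presumes how the contradiction will be settled. The CV12 exception leaves 6 needles open, a shortfall of a quarter.
- **The current range is a further imbalance.** The article says: "The stimulation intensity will vary from 0.1 mA to 1.0 mA for all patients". A range common to all randomized arms is no evidence of a difference between them.
- **The missing Deqi in the control is an error.** It is an openly stated design choice. It does mean that an acupoint versus non-acupoint difference reflects location and Deqi together, which bears on wording only. It does not touch comparisons among the acupoint groups.
- **A fixed number of pairwise tests is affected.** The article lists three null hypotheses and gives no such count. Its third step speaks of the acupoint group in the singular, so a pooled test is possible.

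**Conclusion.** The point holds as an internal contradiction confined to group 3. The needling section states eight needles for each patient and equal stimulation across groups. Its own rules, applied to the two points in Table 2, give 4 needles and 2 pairs, or at most 6 needles and 3 pairs, against 8 and 4 in every other acupuncture arm.

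This rests on two readings of the text: one auxiliary per acupuncture needle, and BL21 needled on one side. Both are stated, and together they reproduce the figure of eight for the four-point arms.

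If group 3 does have fewer needles, its contrasts with groups 1, 2, 4 and the non-acupoint control mix point type with number of stimulated sites and cannot by themselves show acupoint specificity. It would go too far to say that the trial cannot address specificity at all. Comparisons among groups 1, 2 and 4 are not affected by this point, and the group 3 contrasts remain interpretable if labelled for what they compare.

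**What to change.** 1. Reconcile Table 2 with the section on standardized manipulation on the number of needles and stimulated pairs in group 3. Which number applies is for the investigators to settle; none is proposed here.
2. If group 3 has fewer than the other arms, restrict the eight-needle sentence to the arms it fits, and correct the equal-stimulation statements in that section and in the Discussion.
3. In the same case, report group 3 against groups 1, 2, 4 and the non-acupoint control as contrasts that differ in both point type and number of stimulated sites, and do not present them as evidence on acupoint specificity alone.
4. As a secondary wording point, describe the acupoint versus non-acupoint contrast as differing in Deqi as well as location, in line with what the article already discloses.

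The cost is a clarification and, depending on the answer, a narrower claim for one arm. It needs no extra patients, no extra data and no new analysis.
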